**Figure 1 F1:**
[figure not shown]
Participant flow diagram and overview of procedure.

### Setting

The Women’s and Children’s Health Network (WCHN) is the State-wide service responsible for “promoting, maintaining and restoring” the health of women, children and young people in South Australia [22]. Child and Family Health Services (CaFHS) is a key community component of the WCHN and is responsible for providing support for infants, children, and families across the State. To do this, CaFHS provides a full range of nurse home-visiting services, clinic-based nurse services, parent support groups, telephone support, and a specialist residential service for new mothers and infants with high needs.

### Procedure

Staff in birthing hospitals in South Australia ask all new mothers for their consent to be contacted by CaFHS to arrange a health check during their initial postnatal weeks. Approximately 93% of mothers give consent and are subsequently contacted by CaFHS administrative officers who arrange appointments for mothers with nurses either in family homes or at CaFHS clinics. For the purpose of the present study, mothers were advised by hospital staff about the study and the possibility that they may be asked to take part in it.

When subsequently contacted by CaFHS administrative officers, mothers were reminded about the study and verbal consent for their participation was sought. The script used by administration officers to inform mothers of the trial is included in Additional file 1. Mothers who consented were asked if they had a strong preference to participate in the internet-based group or receive standard care. As described above, those who expressed a strong preference for a particular arm of the study were enrolled in their preferred group. Those who did not have a strong preference were randomised to the intervention or standard care groups [23].

The contact details of mothers who gave verbal consent to participate in the study were provided to the research team, who contacted mothers by telephone and explained the study in more detail. Following the telephone call, mothers who confirmed their verbal consent were visited by a research assistant who completed a written consent process and arranged for completion of the 2-month (pre-intervention) assessment. At the time of their pre-intervention assessment, mothers were provided with a username and password for the internet-based intervention and given initial training in the use of the program. When they logged onto the program, mothers were welcomed to their group by the nurse group leader and proceeded with the intervention over the following six months.

### Participants

Participants eligible for the present study were mothers and infants who lived in regions where services are provided by one of six CaFHS clinics in Adelaide. These clinics were chosen because they provide services to a large number of mothers whose socio-demographic characteristics are comparable to the broader population of mothers in metropolitan Adelaide. Mothers were excluded from participation in the study if: (i) they did not have access to the internet, (ii) required an interpreter, or (iii) their nurse/clinician recommended that they not participate due to the presence of problems such as infant ill-health, domestic violence or substance abuse.

During the period of recruitment, 3367 maternal and infant health checks were completed by staff in these clinics. Of these mothers 1123 were not approached due to reasons outside the control of the research team (e.g., during periods of high competing demands, or staff shortages). As a result, during the period of recruitment 2244 were invited to participate and assessed for eligibility for the trial (See Figure 1). Of mothers assessed for eligibility, 354 were not eligible due to lack of internet access, insufficient English skills, or clinician exclusion. This left 1890 mothers of whom 65 subsequently could not be contacted by the research team. Among those who could be contacted (n = 1825), 819 agreed to participate (response rate = 45%).

### Sample size

Our primary outcomes focus on mothers’ sense of competence and self-efficacy in areas relevant to parenting and problem solving with infants. These outcomes were chosen in consultation with CaFHS nurses who identified one of their primary goals as helping ensure parents feel more competent to manage challenges associated with the care of infants.

Given that the primary question for the trial focuses on testing the equivalence of the nurse-moderated group-based internet program versus standard care, we estimated that with a sample size of 200 per randomized group, we would have 80% power at alpha = 0.05 to detect a 0.25 standard deviation difference (inferiority range) between the home-visit and nurse led internet groups in the primary outcome. Thus we would have 80% power to test the hypothesis that the internet-based intervention is no more than 0.25 of a standard deviation inferior when compared to standard care on the primary outcome measures. These estimates were based on data from our current 2 year follow-up of the Nurse Home Visiting program [11]. Based on this earlier study we allowed for an attrition of 20% over 2 years in the present study. To take this into account, we aimed to recruit 240 mothers to be randomised to each study group. Figure 1 shows the participant flows in the study leading to the final trial sample.

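### The target of 240 per group does not preserve 200 after the stated 20% attrition: it leaves 192, a small arithmetic error that takes planned power from about 80% to about 79%

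*Protocol article*

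**What the plan says.** All the figures are in the Sample size section of the protocol article. The authors state that "with a sample size of 200 per randomized group, we would have 80% power at alpha = 0.05", and that the hypothesis to be tested is that "the internet-based intervention is no more than 0.25 of a standard deviation inferior when compared to standard care on the primary outcome measures". On losses they write: "Based on this earlier study we allowed for an attrition of 20% over 2 years in the present study". The next sentence ties the recruitment target to that allowance: "To take this into account, we aimed to recruit 240 mothers to be randomised to each study group". The section gives no other reserve and no formula for the inflation. It refers the reader to Figure 1 for the final sample; that figure is not shown in the text available here.

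**The concern.** Attrition is ordinarily a share of those enrolled, so the number to randomise is the number needed at the end divided by the share retained. The stated target is exactly the number needed increased by 20%, which applies the percentage to the wrong base. If so, the attrition allowance, the recruitment target and the size on which the 80% power rests do not agree with one another.

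What is at stake is how the trial describes its own precision. In a non-inferiority trial, an inconclusive result is judged against the planned margin and power, so those figures should follow from the stated inputs. The base also has little slack: on the reading that reproduces it, 198 per group are needed and 200 were planned, so even a small shortfall takes the plan below its stated 80%.

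**Working it through.** **Inputs from the Sample size section:** 200 per randomised group; 80% power; alpha 0.05; margin 0.25 SD; attrition 20%; target 240 per group. Allocation is taken as 1:1, from the odd/even rule in the Randomisation section.

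**Assumptions, not stated in the article:** alpha is one-sided, the true difference is zero, and the test uses a normal approximation with SD = 1 on the standardised scale.

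**Step 1. Reproduce the 200.** The size per group is n = 2 x ((z for alpha + z for power) / margin)².

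- One-sided 0.05: 2 x ((1.645 + 0.842)/0.25)² = 198 after rounding up. This agrees with the stated 200.
- One-sided 0.025 (two-sided 0.05): 252.
- Two one-sided tests at 0.05 each: 275.

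Of these, only the one-sided 0.05 reading reproduces 200, so it is used below.

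**Step 2. Check the attrition step.**

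- Number needed to keep 200: 200/(1 - 0.20) = 250 per group.
- Increasing 200 by 20%: 200 x 1.20 = 240 per group, which is the stated target.
- Remaining from 240 after a 20% loss: 240 x 0.80 = 192, which is 8 per group short of 200.
- Attrition at which 240 leaves 200: 1 - 200/240 = 16.7%.
- Starting from the unrounded-up need of 198: 198/0.80 = 247.5, so 248. Rounding in the base does not explain 240.

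The target is therefore 10 per group (20 in total) below 250, or 4%.

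**Step 3. Effect on power.** Power = Phi(0.25/sqrt(2/n) - 1.645).

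| n per group | 0.25/sqrt(2/n) | Power |
|---|---|---|
| 200 | 2.500 | 80.4% |
| 198 | 2.487 | 80.0% |
| 192 | 2.449 | 78.9% |

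**Step 4. Effect expressed as a margin.** The margin with 80% power at 192 per group is (1.645 + 0.842) x sqrt(2/192) = 0.254 SD, against the stated 0.25 SD.

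**The case against.** The strongest reply is that the three figures can be reconciled through the time horizon. The 20% is given over 2 years, whereas assessments run from before 2 months of age to 21 months. If follow-up is taken as about 20 months (an assumption), a proportional share of a 24-month loss is 20% x 20/24 = 16.7%, which leaves exactly 200 of 240. With a constant loss rate, 0.80^(20/24) = 0.830 are retained, or about 199. The arithmetic is right, but the article does not say this. It says that "we allowed for an attrition of 20% over 2 years in the present study", which applies the 20% to this trial's own follow-up, and it then gives 240 as the number that takes this into account. The scaling remains a possible explanation that the authors could state; as written, the figure is wrong.

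A second reply is that the consequence is slight, and this stands. Power falls by about 1.5 points against 200 per group and about 1 point against the stated 80%.

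A third is that 192 is not the number analysed. This also stands. The Analysis plan specifies intention-to-treat and a longitudinal GEE analysis over repeated assessments, so a mother lost after the 9- or 15-month visit can still contribute data. The 192 is the number remaining at the end of follow-up.

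**Conclusion.** The point holds as a minor arithmetic error. With 20% attrition, 240 per group leaves 192 at the end of follow-up; 200 would need 250, and 240 covers 16.7%. That part needs only the article's own figures and the ordinary meaning of attrition. The size of the effect (78.9% against 80.4% power, or 80% power at 0.254 SD) also depends on a one-sided 5% test and a true difference of zero, neither of which is stated.

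Three stronger readings are not supported.

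- A reader might infer that the trial is materially underpowered by this slip. A loss of about one point from the stated 80% does not show that.
- A reader might infer that the trial fell short in fact. The 819 recruited include mothers allocated by preference, and the numbers randomised are not in the text available here, so the achieved size cannot be checked.
- A reader might add the shortfall to losses from clustering by nurse or from having two primary outcomes. The article gives no intracluster correlation and describes clustering as often small, and no such loss has been computed here. Those would be separate questions.

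**What to change.** The Objectives section says that recruitment was completed in December 2013, so the target cannot be changed and the remedy is to restate the figure in one of two ways.

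1. Keep the 20%: say that 240 randomised per group with 20% attrition leaves 192 per group with complete follow-up and about 79% power for a 0.25 SD margin. State the sidedness of alpha and the assumed true difference beside it, since the 79% depends on both.
2. Keep the 200: say that 240 per group allows for 16.7% attrition. If a shorter follow-up than 2 years is the reason for the lower rate, say so.

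Either way the cost is one sentence and no further enrolment. The first option lowers the stated power by about one point; the second lowers the stated attrition allowance from the 20% taken from the earlier study.

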### Randomisation

Randomisation was based on the service identification number serially assigned to all infants when they are referred to CaFHS from their birthing hospital (assignment is done by central administrative CaFHS staff who had no involvement in recruitment of mothers, delivery of the intervention, or the analysis of results for the study). Mothers of infants with an odd service identification number were assigned to the intervention group. Mothers of infants with an even service identification number were assigned to the comparison group. We used this approach because CaFHS administration officers recruited mothers to the trial in the course of their normal work responsibilities, and because this trial was pragmatic by design we judged this method as being desirable because it demonstrated that randomisation could be done within normal workflows. However, this placed an additional burden on administrative staff in circumstances where they were already busy with a range of tasks. Despite this, they agreed to recruit mothers provided that the additional time demands were kept to manageable proportions. The use of a more traditional randomisation approach had the potential to increase recruitment time and interfere with administrative officers’ routine work. For this reason we chose to utilise the infant’s identification number, which was readily available to the administrative officers, to determine the group to which mothers with no strong preference were assigned.

The research team was blind to group allocation at the time of recruitment and assignment of mothers to the study groups. However due to the nature of the intervention, after the intervention commenced, it was not possible to keep research staff blind to the groups to which mothers had been allocated.

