**Methods/Design:**

The evaluation utilised a pragmatic preference randomised trial comparing the equivalence of outcomes for mothers and infants across the two study groups. Eligible mothers were those whose services were provided by nurses working in one of six community clinics in the metropolitan region of Adelaide. Mothers were excluded if they did not have internet access, required an interpreter, or their nurse clinician recommended that they not participate due to issues such as domestic violence or substance abuse. Randomisation was based on the service identification number sequentially assigned to infants when referred to the Child and Family Health Services from birthing units (this was done by administrative staff who had no involvement in recruiting mothers, delivering the intervention, or analyzing results for the study). Consistent with design and power calculations, 819 mothers were recruited to the trial. The primary outcomes for the trial are parents’ sense of competence and self-efficacy measured using standard self-report questionnaires. Secondary outcomes include the quality of mother-infant relationships, maternal social support, role satisfaction and maternal mental health, infant social-emotional and language development, and patterns of service utilisation. Maternal and infant outcomes will be evaluated using age-appropriate questionnaires when infants are aged <2 months (pre-intervention), 9, 15, and 21 months.

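### Allocation by odd or even service number could be foreseen by the officers who sought consent and asked about preference, so the no-preference comparison is quasi-randomised and not concealed from them

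*Protocol article*

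**What the plan says.** The Randomisation section of the protocol article ties allocation to a number that exists before any study contact: "Randomisation was based on the service identification number serially assigned to all infants when they are referred to CaFHS from their birthing hospital". The rule is fixed in both directions: "Mothers of infants with an odd service identification number were assigned to the intervention group", and "Mothers of infants with an even service identification number were assigned to the comparison group".

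The same section says that "CaFHS administration officers recruited mothers to the trial in the course of their normal work responsibilities". It explains that the infant's number was chosen because it fitted their workload, describing it as a number "which was readily available to the administrative officers, to determine the group to which mothers with no strong preference were assigned".

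The Procedure section describes the officers' contact: "When subsequently contacted by CaFHS administrative officers, mothers were reminded about the study and verbal consent for their participation was sought". It continues: "Mothers who consented were asked if they had a strong preference to participate in the internet-based group or receive standard care". Mothers with a strong preference received their chosen programme; only the others entered the randomised comparison. The research team's explanatory call and written consent came afterwards.

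Two reassurances are offered. The abstract, after describing the sequential numbering, adds that "this was done by administrative staff who had no involvement in recruiting mothers, delivering the intervention, or analyzing results for the study". The Randomisation section says that the research team was blind to allocation at recruitment and assignment. It makes no such statement about the administration officers.

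**The concern.** Concealment means that whoever decides on a participant's entry cannot foresee the arm. Here the arm follows from the last digit of a number that the recruiters could read. Three gates lie before entry to the randomised comparison: whether a mother is approached, whether she gives verbal consent, and whether her answer counts as a strong preference. The third is the softest. A lukewarm leaning could be recorded as strong, or not, depending on whether the number would give her the programme she leans towards.

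If that happened, the two no-preference arms would differ at entry. The non-inferiority comparison would carry the difference, and so would the planned comparison of randomised with preference groups, which uses the same classification. The intention-to-treat principle in the Analysis plan protects the groups after entry; it cannot undo selection before it.

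**Working it through.** **Who did what**

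| Step | Who | Arm foreseeable? |
|---|---|---|
| Number issued at referral | Central staff with no part in recruitment (Randomisation) | Arm becomes fixed here |
| Approach, verbal consent, strong-preference question | Officers' contact (Procedure); number readily available to them (Randomisation) | Yes, from parity |
| Placement of no-preference mothers | By the number available to the officers (Randomisation) | Yes |
| Explanatory call, written consent, pre-intervention assessment | Research team, blind at recruitment and assignment | After assignment |

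The uninvolved staff issue the number. That stops recruiters from influencing it but does not stop them from reading it.

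**How much passes through the gates** (Participants section)

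- Not approached: 1123 of 3367 health checks.
- Contactable but not recruited: 1825 − 819 = 1006. The article does not say how many of these were lost after assignment.

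**Reproducing the design figure** (Sample size section: 200 per group, 80% power, alpha 0.05, margin 0.25 SD)

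- n per arm = 2 × (1.645 + 0.842)² / 0.25² = 198 for a one-sided 5% test with no true difference, close to the stated 200.
- Power at 200 per arm: SE = √(2/200) = 0.10 SD; Φ(0.25/0.10 − 1.645) = 80.4%.
- The article does not state sidedness. A one-sided 2.5% test would need 252 per arm, so one-sided 5% is the reading that reproduces 200. It is used below as an assumption.

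**Effect of a shift b in the arm contrast.** The documents give no size for b, so the values are assumed. As a guide, b = 0.05 SD arises if 10% of one arm's potential entrants, differing from the rest by 0.5 SD, are steered out (0.10 × 0.5). If they differ by 1 SD, b = 0.10 SD.

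- Shift towards the internet arm, true difference at the margin: false non-inferiority = Φ(b/0.10 − 1.645).
- Shift against the internet arm, no true difference: power = Φ((0.25 − b)/0.10 − 1.645).

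| Assumed b (SD) | False non-inferiority | Power |
|---|---|---|
| 0 | 5.0% | 80.4% |
| 0.025 | 8.2% | 72.7% |
| 0.05 | 12.6% | 63.9% |
| 0.10 | 26.0% | 44.2% |

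**Precision of an analysis of all 819 by parity.** Mothers with a strong preference receive their programme whatever the number, so parity moves the programme only in the no-preference group. Assume that 480 of the 819 were randomised (the recruitment target, 2 × 240) and that 20% are lost.

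- SE with parity as instrument = √(4/(819 × 0.8)) / (480/819) = 0.0781 / 0.586 = 0.133 SD.
- SE in the randomised group alone = √(2/192) = 0.102 SD, where 192 = 240 × 0.8.

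**The case against.** The method is disclosed, and a reason is given: recruiting within routine workflow without overloading the officers. The order in the Procedure section is consent, then the preference question, then assignment of those without a strong preference, so on paper the number is used after classification. Recruiters could not alter the number, and its parity is probably unrelated to prognosis when issued. The officers' script (Additional file 1) and the flow diagram are not shown.

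Much of this stands, and it rules out several stronger readings.

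- A reader might infer that officers knew the arm before classifying a mother, or steered mothers. No section says so. They could have known; that is all the text supports.
- A reader might call the abstract false. Its remark about uninvolved staff follows directly on the numbering and can be read as referring only to that, which agrees with the Randomisation section. It is ambiguous and easily taken as a concealment safeguard, which it is not.
- A reader might call the scheme alternation. The serial number runs over all infants referred to the service, while recruits come from six clinics, so enrolled mothers need not alternate. The weakness is that parity is visible.
- A reader might assume that bias would favour the internet arm. Nothing indicates a direction.

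What the objection does not answer is the access itself. Workload explains why the method was chosen but supplies no concealment, and the stated order does not prevent a number on hand from being read earlier.

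**Conclusion.** The point holds as one of foreseeable allocation. The arm was determined by a number readily available to the people who handled the gates to the randomised comparison, and no safeguard in the article applies to them. Whether selection occurred, in which direction and how strongly cannot be told from the document.

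The size is illustrative only. It rests on an assumed one-sided 5% test, 200 analysed per arm and an assumed shift. With a margin of 0.25 SD, a shift of one fifth of the margin (0.05 SD) is enough to matter: false non-inferiority of 12.6% instead of 5%, or power of about 64% instead of about 80%. At 0.10 SD the figures are 26% and about 44%. Confidence is high on the mechanism; none is claimed on occurrence or magnitude.

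**What to change.** Recruitment closed in December 2013 (Objectives), so allocation cannot be changed. Follow-up was still under way, which leaves room for these steps.

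1. **Label.** Describe the no-preference comparison as quasi-randomised by service-number parity and not concealed from the recruiting officers. Reword the abstract to say that the uninvolved staff only issued the number.
2. **Check.** Among the 819, tabulate strong preference, its direction and baseline scores by parity. An association would signal steering. Where service records are available and may be used, add approach, consent and loss before written consent. The Procedure section says that details of mothers who gave verbal consent went to the research team, so records on other mothers may not be held.
3. **Adjust.** Include the pre-intervention score of the outcome in the primary model, if the SAP (not shown) does not already do so. This removes only the imbalance that the score captures.
4. **Sensitivity analysis.** Compare all 819 by parity, with parity as instrument for the programme allocated. State that this addresses steering at the preference question only. If approach, consent or loss depended on parity, the 819 are already selected and the instrument does not cure it.

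The cost is wording, one table and one further analysis, mostly from data collected for the trial. The parity analysis is less precise (SE about 0.13 against 0.10 SD if 480 of 819 were randomised, an assumption), so it belongs beside the primary comparison, not in its place.
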